### Endpoints and Assessments

At baseline, the following data are collected: patient demography, vital parameters, physical status, prior and concomitant diseases and medications, MS diagnosis, MS history (including prior relapses), prior MS treatment, reason for initiating/switching to ozanimod, and treatment modalities with ozanimod. In addition, physician-reported outcomes [EDSS (10) and Symbol Digit Modalities Test (SDMT) (12, 13)] and patient-reported outcomes (PROs; Treatment Satisfaction Questionnaire for Medication, version 1.4 (TSQM v1.4) (14, 15), United Kingdom Neurological Disability Rating Scale (UKNDS) (16, 17), Multiple Sclerosis Quality of Life Instrument-54 items (MSQOL-54) (18), Fatigue Scale for Motor and Cognitive Functions (FSMC) (19), Work Productivity and Activity Impairment Questionnaire for Multiple Sclerosis, version 2.1 (WPAI-MS v2.1) (20), and Multiple Sclerosis Health Resource Utilization Survey, version 3.0 (MS-HRS v3.0) (21) are completed. Following the baseline visit, these physician-reported outcomes and PROs, together with physician-reported clinical relapses (the occurrence of new symptoms or the worsening of old symptoms) are completed at 3-, 6-, or 12-month intervals during the 60-month observation period (Table 2). Alternate forms of the SDMT will be used to avoid practice effects. The following characteristics of ozanimod treatment are documented continuously: initial dose escalation; maintenance dose; temporary interruptions of treatment, including date and reason for interruption, and re-initiation of therapy following treatment interruption; and all medication taken concomitantly with ozanimod and all changes in concomitant medication during the study, including reason for administration. Primary and secondary endpoints are summarized in Table 3.

**Table 2 T2:** Schedule of enrollment, interventions, and assessments.

**Assessment/Data Collected**	**Observation**				**End of observation^a^**	**Safety follow-up^b^**
	**Enrollment**	**Month 1**	**Month 3–24**	**Month 24–60**		
						**Last treatment +**
	**Baseline**		**Every 3 months**	**Every 6 months**	**End of study**	**3–8 months**
**Baseline**						
Informed consent	X					
Inclusion/exclusion criteria	X					
Demography	X					
General medical history	X					
MS history and pretreatment^c^	X					
Concomitant diseases	X					
All previous malignant diseases	X					
All other previous diseases within 5 years	X					
prior to study enrollment
Physical status^d^	X					
**Treatment**						
Treatment modalities^e^	X	X	X	X		X
Concomitant medication	X	X	X	X		X
Subsequent MS treatment					X	X
**Physician-reported assessment**						
Persistence with therapy	Assessed continuously throughout study					
Clinical relapse (ARR)		X	X^f^	X^f^		X
EDSS	X	X	X^f^	X^f^		X
SDMT	X	X^g^	X^g^	X		X
MRI^h^	X^h^	X^h^	X^h^	X^h^		X^h^
**Patient-reported assessment**						
Adherence to therapy^i^	X^i^	X^i^	X^i^	X^i^	X^i^	X^i^
TSQM v1.4	X	X	X^j^	X		X
UKNDS	X	X	X^g^	X		X
MSQOL-54	X	X	X^g^	X		X
FSMC	X	X	X^g^	X		X
WPAI-MS v2.1	X	X	X^g^	X		X
MS-HRS v3.0	X	X	X^g^	X		X
**Safety assessment**						
AEs/SAEs	Assessed continuously throughout study					
Laboratory panel^h^	X^h^	X^h^	X^h^	X^h^		X^h^

*AE, adverse event; ARR, annualized relapse rate; EDSS, Expanded Disability Status Scale; FSMC, Fatigue Scale for Motor and Cognitive Functions; MRI, magnetic resonance imaging; MS, multiple sclerosis; MSFC, Multiple Sclerosis Functional Composite; MS-HRS v3.0, Multiple Sclerosis Health Resource Survey, version 3.0; MSQOL-54, Multiple Sclerosis Quality of Life-54; SAE, serious adverse event; SDMT, Symbol Digit Modalities Test; TSQM v1.4, Treatment Satisfaction Questionnaire for Medication, version 1.4; UKNDS, United Kingdom Neurological Disability Rating Scale; WPAI-MS v2.1, Work Productivity and Activity Impairment Questionnaire for Multiple Sclerosis, version 2.1*.

a *Documentation performed directly after a patient reached the regular end of study (at month 60) or permanently discontinued ozanimod treatment before month 60; if routine data were collected that do not meet any of the documentation time points offered, these data may be entered with the month 60 documentation*.

b *Follow-up documentation of potential AEs and subsequent therapy, performed approximately 3–8 months after stopping treatment with ozanimod and when a new MS therapy is initiated, or after 8 months (at the latest) if there is no subsequent MS therapy initiated*.

c *Includes MS diagnosis according to International Classification of Diseases, Tenth Revision; first manifestation of MS; course of MS disease and number of relapses within the year before enrollment; and type and duration of prior disease-modifying therapies for MS*.

d *Includes vital parameters, physical status*.

e *Treatment modalities referring to ozanimod, including (planned) date of first administration of ozanimod, reason for switch to ozanimod, interruptions, re-initiation of therapy following treatment interruption, and reason for discontinuation in case of switch to another MS treatment*.

f *At yearly intervals (months 12, 24, 36, 48, and 60) only*.

g *At 6-month intervals (months 6, 12, 18, and 24) only*.

h *Only if available based on the local clinical routine assessments performed at the study center: MRI (number of lesions) and relevant laboratory measurements, especially those for monitoring ozanimod therapy (e.g., liver parameters, such as alanine aminotransferase, aspartate aminotransferase, gamma-glutamyl transferase, and total bilirubin; differential blood count; or lymphocyte count)*.

i *Patient-reported qualitative assessment of how often the patient missed doses and how regularly he or she took the medication, by entering the date of starting with a new ozanimod package and selection of the package size. This information is collected electronically via the patient portal application or, alternatively, using paper-based questionnaires provided at the local study center*.

j *At 3-month intervals (month 3, 6, 9, 12, 15, 18, 21, and 24)*.

**Table 3 T3:** Primary and secondary endpoints in the OzEAN study.

**Domain**	**Reported by**	**Assessment**	**Outcome measure**	**Time point**
**Primary endpoint**				
Treatment satisfaction	Physician	Persistence with therapy	• Proportion of patients who remain on continuous treatment with ozanimod • Evaluated at month 60	Collected continuously
**Secondary endpoints**				
Treatment satisfaction	Physician	Persistence with therapy	• Proportion of patients who remain on continuous treatment with ozanimod • Evaluated at months 12, 24, 36, and 48	Collected continuously
	Patient	Adherence to therapy	• Percentage of dose taken as prescribed • Evaluated at months 12, 24, 36, 48, and 60	Months 3, 6, 9, 12, 15, 18, 21, 24, 30, 36, 42, 48, 54, and 60, and SFU
	Patient	TSQM v1.4	• Changes in TSQM v1.4 domains • Relationship between each TSQM v1.4 domain and clinical outcomes^a^	Baseline and months 3, 6, 9, 12, 15, 18, 21, 24, 30, 36, 42, 48, 54, and 60, and SFU
Effectiveness	Physician	Clinical relapse	• Annualized relapse rate	Months 12, 24, 36, 48, and 60, and SFU
	Physician	EDSS	• Change from baseline in EDSS	Baseline and months 12, 24, 36, 48, and 60, and SFU
	Patient	UKNDS	• Change from baseline in UKNDS sum score • Proportion of patients with a clinically meaningful improvement/worsening of 1 grade in each subscale	Baseline and months 6, 12, 18, 24, 30, 36, 42, 48, 54, and 60, and SFU
Cognitive processing speed	Physician	SDMT	• Change from baseline in SDMT • Proportion of patients with: ° Increase in raw score of ≥ 4 points or 10% from baseline (improved) ° Decline in raw score of ≥ 4 points or 10% from baseline (worsened) ° Raw score change from baseline who do not meet improved or worsened definition (stable)	Baseline and months 6, 12, 18, 24, 30, 36, 42, 48, 54, and 60, and SFU
QoL	Patient	MSQOL-54	• Change from baseline in PCS and MCS • Proportion of patients with: ° Increase of ≥ 5 points in PCS and/or MCS (improved) ° Decline of ≥ 5 points in PCS and/or MCS (worsened)	Baseline and months 6, 12, 18, 24, 30, 36, 42, 48, 54, and 60, and SFU
Fatigue	Patient	FSMC	• Change from baseline in FSMC sum score and physical and cognitive subdomains • Proportion of patients with: ° Decline of ≥ 10 points in sum score (improved) ° Increase of ≥ 10 points in sum score (worsened) ° Decline of ≥ 6 points or ≥ 5 points in cognitive and/or physical domain, respectively (improved) ° Increase of ≥ 6 points or ≥ 5 points in cognitive and/or physical domain, respectively (worsened)	Baseline and months 6, 12, 18, 24, 30, 36, 42, 48, 54, and 60, and SFU
Health economics	Patient	WPAI-MS v2.1	• Change from baseline in WPAI-MS v2.1 domains	Baseline and months 6, 12, 18, 24, 30, 36, 42, 48, 54, and 60, and SFU
	Patient	MS-HRS v3.0	• Resource use/direct and indirect costs	Baseline and months 6, 12, 18, 24, 30, 36, 42, 48, 54, and 60, and SFU
Safety	Physician	Incidence rate for AEs^b^	• Number of new cases per population at risk over the follow-up period (per person-time) • Number of patients with event	Collected continuously

*AE, adverse event; EDSS, Expanded Disability Status Scale; FSMC, Fatigue Scale for Motor and Cognitive Functions; MCS, mental health composite summary; MS-HRS v3.0, Multiple Sclerosis Health Resource Survey, version 3.0; MSQOL-54, Multiple Sclerosis Quality of Life-54; PCS, physical composite summary; SDMT, Symbol Digit Modalities Test; TSQM v1.4, Treatment Satisfaction Questionnaire for Medication, version 1.4; UKNDS, United Kingdom Neurological Disability Rating Scale; QoL, quality of life; SFU, safety follow-up; WPAI-MS v2.1, Work Productivity and Activity Impairment Questionnaire for Multiple Sclerosis, version 2.1*.

a *If effect size Cohen's d (used to indicate the standardized difference between 2 means) > 0.3*.

b *Based on the first occurrence of event during the follow-up period*.

The primary endpoint is persistence with therapy (as reported by physicians), defined as the proportion of patients who remain on continuous treatment with ozanimod (with gaps of ≤ 90 days allowed), from baseline to month 60. Persistence from baseline to months 12, 24, 36, and 48 is a secondary endpoint. Adherence to therapy, defined as the percentage of ozanimod doses taken as prescribed (as reported by patients) (22), at months 3, 6, 9, 12, 15, 18, 21, 24, 30, 36, 42, 48, 54, and 60, and at the safety follow-up, is a secondary endpoint.

Additional secondary endpoints include the following physician-reported outcomes: clinical relapse, expressed as ARR at months 12, 24, 36, 48, and 60, and at the safety follow-up (total number of relapses experienced by all patients in this study divided by the total number of days in the study for the patients, and the ratio multiplied by 365); disability, assessed as change in EDSS score from baseline to months 12, 24, 36, 48, and 60, and at the safety follow-up; and cognitive processing speed, measured using the SDMT and quantified as change from baseline in SDMT score, proportion of patients with increase (improvement) or decrease (worsening) in SDMT raw score of ≥ 4 points or 10% from baseline, and proportion of patients with change in SDMT raw score that does not meet criteria for improvement or worsening (stable) at months 6, 12, 18, 24, 30, 36, 42, 48, 54, and 60, and at the safety follow-up.

Secondary endpoints reported by patients (i.e., PROs) include measures of treatment satisfaction, effectiveness, QoL, fatigue, and health economics. Treatment satisfaction is assessed using the TSQM v1.4; secondary endpoints are changes in TSQM v1.4 domains (effectiveness, side effects, convenience, and global satisfaction) and the relationship between each domain and clinical outcomes at months 3, 6, 9, 12, 15, 18, 21, 24, 30, 36, 42, 48, 54, and 60, and at the safety follow-up. Disability is assessed using the UKNDS; secondary endpoints are the change from baseline in UKNDS sum score and the proportion of patients with clinically meaningful improvement or worsening of at least 1 grade in each UKNDS subscale at months 6, 12, 18, 24, 30, 36, 42, 48, 54, and 60, and at the safety follow-up. QoL is assessed using the MSQOL-54; secondary endpoints are change from baseline in the physical composite summary (PCS) and mental health composite summary (MCS) scores, and the proportion of patients with a clinically meaningful change [increase (improvement) or decrease (worsening) of ≥5 points] (23) in PCS or MCS score, at months 6, 12, 18, 24, 30, 36, 42, 48, 54, and 60, and at the safety follow-up. Fatigue is assessed using the FSMC; secondary endpoints include change from baseline in FSMC sum score, physical subscale, and cognitive subscale; proportion of patients with decrease (improvement) or increase (worsening) of ≥10 points in the sum score; proportion of patients with decrease (improvement) or increase (worsening) of ≥6 points in the cognitive domain; and proportion of patients with decrease (improvement) or increase (worsening) of ≥5 points in the physical domain, at months 6, 12, 18, 24, 30, 36, 42, 48, 54, and 60, and at the safety follow-up. Measures of health economics include the WPAI-MS v2.1 and the MS-HRS v3.0; secondary endpoints are the change from baseline in WPAI-MS v2.1 domains at months 6, 12, 18, 24, 30, 36, 42, 48, 54, and 60, and at the safety follow-up, and resource use and direct and indirect costs assessed using the MS-HRS v3.0 at baseline and months 6, 12, 18, 24, 30, 36, 42, 48, 54, and 60, and at the safety follow-up.

Incidence of AEs [number of new cases per population at risk over the follow-up period (per person-time) and number of patients with event] is also a secondary endpoint. AEs are defined as any untoward medical occurrence, which does not necessarily have a causal relationship with treatment.

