### Eligibility Criteria

Eligible patients are adults (≥18 years of age) diagnosed with RRMS who are either treatment-naive or have prior experience with a disease-modifying therapy and elected to switch to ozanimod. Patients with contraindications specified in the current version of the SmPC (3), or with known hypersensitivity to ozanimod or any of its excipients, are excluded. Patients may not be participating in any other clinical studies.

Inclusion and exclusion criteria are shown in Table 1.

**Table 1 T1:** Eligibility criteria.

**Inclusion Criteria**	**Exclusion Criteria**
Males or females aged ≥ 18 years who provided written informed consent	Contraindications specified in the current version of the SmPC
Confirmed diagnosis of RRMS according to ICD-10 and eligible for treatment with ozanimod according to physician's judgement and based on the recommendation of the current SmPC	Known hypersensitivity to the active substance(s) or to any of the excipients of ozanimod as specified in the SmPC
The decision to initiate treatment with ozanimod must have been made by the treating physician before enrollment and independently of this study; retrospective documentation of ozanimod therapy and enrollment of patients that are already on ozanimod therapy is not allowed	Participation in any other clinical studies

*ICD-10, International Statistical Classification of Diseases and Related Health Problems, 10^th^ version; RRMS, relapsing-remitting multiple sclerosis; SmPC, Summary of Product Characteristics*.

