**Patient-Reported Assessment**	
Treatment Satisfaction Questionnaire for Medication, version 1.4 (TSQM v1.4) (14, 15)	The TSQM v1.4 is a general measure of treatment satisfaction with medication in chronic diseases that has been tested extensively in people with RRMS. It comprises 14 items covering 4 domains: effectiveness, side effects, convenience, and global satisfaction. On individual items, patients rate their satisfaction with a medication, presence/absence and bothersomeness of side effects, extent to which side effects interfere with functioning and impact treatment satisfaction, ease of use and convenience, and confidence in the treatment. Ratings reflect experience with the medication over the previous 2–3 weeks, or since the patient's last use of the medication. Scores range from 0 to 100, with higher scores representing greater satisfaction.
United Kingdom Neurological Disability Rating Scale (UKNDS) (16, 17)	The UKNDS is a simple, user-friendly clinical disability scale that is valid and reliable for the assessment of patients with MS. It is derived from Guy's Neurology Disability Scale and consists of 11 domains: cognition, mood, vision, speech, swallowing, upper limb function, lower limb function, bladder function, bowel function, fatigue, and pain. Each subscale is scored on a 6-point Likert scale ranging from 0 (normal) to 5 (total loss of function/maximum impairment), producing an overall sum score ranging from 0 (best) to 55 (worst). Improvement or worsening of at least 1 grade in each subscale are considered clinically meaningful.

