Medication adherence (secondary endpoint) will be evaluated categorically in terms of the percentage of doses taken as prescribed.

Secondary endpoints of clinical effectiveness (ARR, EDSS, and SDMT) and all PRO measures (changes from baseline, including proportion of patients who achieved a clinically meaningful change from baseline) will be analyzed descriptively. For TSQM v1.4, it is assumed that a clinically meaningful relationship between TSQM v1.4 domains and clinical outcomes is given if the effect size (Cohen's d) is > 0.3 (15).

All AE data will be listed and summarized. AEs will be classified using the Medical Dictionary for Regulatory Activities (MedDRA) classification system. The incidences based on the patient population enrolled as well as incidence density rates (number of events/sum of person-time in years) of all AEs, serious AEs (SAEs), adverse drug reactions (ADRs), and serious ADRs will be summarized by system organ class, preferred term, and relationship to study treatment. AEs leading to discontinuation from treatment will also be summarized and listed separately.

SAS software version 9.2 or higher will be used for analyses.

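### Change from baseline in TSQM v1.4 is undefined for treatment-naive patients and compares two different drugs in switchers

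*Protocol article*

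**What the plan says.** The TSQM row of Table 3 (protocol article, Secondary endpoints) reads "Changes in TSQM v1.4 domains" and gives baseline, 14 visits from month 3 to month 60, and the safety follow-up as time points. The Endpoints and Assessments section also puts the TSQM among the questionnaires completed at baseline. Table 2 schedules it at baseline, at month 1, every 3 months from month 3 to month 24, in the later 6-monthly period, and at the safety follow-up.

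The Statistical Methods section sets the reference point for this whole class of outcomes: "all PRO measures (changes from baseline, including proportion of patients who achieved a clinically meaningful change from baseline) will be analyzed descriptively". Data Collection Methods counts the TSQM among these outcomes.

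Three further statements matter:

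- Table 4 on what the instrument measures: "Ratings reflect experience with the medication over the previous 2–3 weeks". The sentence goes on to allow, as an alternative, the period since the medication was last used.
- Table 1 on when baseline falls: "retrospective documentation of ozanimod therapy and enrollment of patients that are already on ozanimod therapy is not allowed". Footnote e of Table 2 allows the first ozanimod dose to be only a planned date.
- Eligibility Criteria on who enters: patients are "either treatment-naive or have prior experience with a disease-modifying therapy".

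**The concern.** Most of the other scales with a change endpoint (EDSS, SDMT, UKNDS, MSQOL-54, FSMC, WPAI-MS) describe the patient's state, which exists before treatment, so a pre-drug baseline is the natural reference for them. The TSQM is different because its score belongs to a particular medication. A rule written for the whole class gives it a reference that either does not exist or belongs to another drug.

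At stake is what readers will take from a treatment-satisfaction result. The Discussion presents the TSQM as an index of treatment satisfaction, and the Introduction says the patient-reported data are of interest to German authorities for Health Technology Assessment. A mean change from baseline in TSQM would naturally be read there as ozanimod satisfaction rising or falling over time, and it does not measure that.

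**Working it through.** The plan states no figure for the TSQM endpoint, so there is none to reproduce. The check is mainly one of definitions, followed by a rough estimate of how many patients are affected.

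**Step 1: what a baseline TSQM score can refer to.** Patients already on ozanimod cannot enrol, and the first dose may still lie ahead at the baseline visit. Even if the first dose falls on that day, a recall period of 2–3 weeks contains no ozanimod experience. So:

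- Treatment-naive patient: no disease-modifying therapy has been used, neither in the past 2–3 weeks nor at any last use. The score has no stated object.
- Switcher: the score is a valid rating of the previous therapy, because the clause on last use covers it.

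Nothing in the article says which medication the baseline questionnaire refers to, excuses naive patients from it, or names an on-ozanimod visit as the reference.

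**Step 2: what the change score then contains.** Write O(t) for the ozanimod score at visit t, O(1) for the first on-ozanimod score, and P for the score of the prior drug.

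- Switcher: O(t) − P = [O(t) − O(1)] + [O(1) − P]. The first bracket is the course of satisfaction on ozanimod. The second is a contrast between two drugs, and the patient carries it unchanged into every visit.
- Naive patient: P does not exist, so O(t) − P is undefined. Only O(t) and O(t) − O(1) can be formed.

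A pooled change from baseline is thus either a switcher-only result presented as the whole cohort, if naive patients leave the form blank, or a mixture that includes scores with no known object, if they complete it.

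**Step 3: the safety follow-up.** Table 3 includes this time point for the TSQM. Under Study Setting and Treatment it takes place after the last ozanimod dose, when a new MS therapy starts or at 8 months at the latest. The medication being rated is again unclear.

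**Step 4: how many patients.** The article does not state the expected mix. The Sample Size section assumes 5-year persistence of 55% overall, 50% in switchers and 55–60% in naive patients. With naive share w and naive persistence p:

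0.50(1 − w) + p·w = 0.55, so w = 0.05 / (p − 0.50)

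| p (naive) | w | of 1,300 |
|---|---|---|
| 0.60 | 0.05/0.10 = 0.50 | 650 |
| 0.575 | 0.05/0.075 = 0.67 | 867 |
| 0.55 | 0.05/0.05 = 1.00 | 1,300 |

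These inputs are rounded. If the overall 55% stood for 54.5%, the lowest share would be 0.045/0.10 = 0.45, or 585 of 1,300. The result indicates a substantial group and does not estimate its size.

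**Step 5: the first on-ozanimod assessment.** Table 2 lists the TSQM at month 1. Table 3, and the text on patient-reported secondary endpoints, start at month 3. The two must agree before a reference visit can be named.

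**The case against.** The best counter-argument is that the endpoint row does not say baseline. In Table 3 the EDSS, UKNDS, SDMT, MSQOL-54, FSMC and WPAI-MS rows all specify change from baseline, and the TSQM row conspicuously does not. The link comes from one general parenthesis in Statistical Methods, and that parenthesis does not fit every questionnaire: the MS-HRS has no change endpoint. The reference visit and the handling of questionnaires that do not apply could also be left to an analysis plan that is not shown.

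The first part stands as a limit: Table 3 alone does not define a change from baseline. It does not remove the point. The Statistical Methods sentence covers all patient-reported outcomes, baseline is a listed TSQM time point, and no other reference is given. Followed as written, the rule produces the faulty score. That makes it a stated rule that misleads, not a detail left out.

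Three stronger readings are tempting, and the article does not support them:

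- *The switchers' change measures dislike of the drug they left.* The reason for switching is recorded and need not be dissatisfaction. The change is a contrast with prior therapy in patients selected for leaving it, and it is legitimate if labelled so.
- *The naive-versus-switch subgroup analysis is meaningless for the TSQM.* That analysis is planned in general terms and not tied to change from baseline. On-ozanimod scores, and changes between on-ozanimod visits, can be compared between the two groups.
- *At least 650 patients must lack a baseline.* That figure back-solves rounded planning guesses and does not establish a minimum.

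It is also true that the study is descriptive, without hypotheses or P values, and that this is one secondary endpoint among many.

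**Conclusion.** The point holds in a limited form. Under the Statistical Methods rule, a TSQM change from baseline is undefined in treatment-naive patients, and in switchers it is a between-drug contrast. Pooled, it does not describe satisfaction with ozanimod over time. No baseline TSQM score reflects ozanimod experience, but switchers' baseline scores remain valid ratings of their earlier therapy, and all on-treatment data remain usable.

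The conclusion rests on the article's own account of the instrument, the bar on enrolling patients already treated, and the eligibility of naive patients. It does not depend on the naive share, which is unstated; roughly half or more is an assumption drawn from the planning rates. The consequence is confined to one secondary descriptive endpoint. The primary persistence endpoint is untouched.

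**What to change.** 1. In Statistical Methods, exempt the TSQM from the change-from-baseline rule.
2. Make TSQM domain scores by on-ozanimod visit the main summary, overall and in the naive and switch subgroups.
3. Take any change from the first available on-ozanimod assessment. Reconcile Table 2 (month 1) with Table 3 (from month 3) so that this visit is unambiguous. Fixing month 3 as the reference without doing so would overlook the month 1 assessment in Table 2 and restrict the change to patients who persist to month 3.
4. Show the contrast between baseline and on-treatment scores only in switchers, labelled as a comparison with prior therapy and read alongside the recorded reason for switching.
5. Report TSQM scores from the safety follow-up separately, because patients are then off ozanimod.

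The cost is wording in one section and two tables; no new data are needed beyond what Table 2 already schedules. The drawback is that patients who stop before their first on-treatment assessment contribute no change score. They may well differ from those who continue, so their number should be reported next to the result.

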Multiple Sclerosis Quality of Life-54 (MSQOL-54) (18)	The MSQOL-54 is a multidimensional health-related QoL measure that combines both generic and MS-specific items into a single instrument. The generic component is the Short Form-36 Health Survey (SF-36) (42), to which 18 items were added to identify MS-specific issues. There are 54 items distributed into 12 subscales (physical function, role limitations-physical, role limitations-emotional, pain, emotional well-being, energy, health perceptions, social function, cognitive function, health distress, overall quality of life, and sexual function), along with 2 summary scores (physical composite summary [PCS] and mental health composite summary [MCS]). A change in score equivalent to 0.5 SD has been found to have almost universal relevance as a minimum clinically important difference for health-related QoL. Using the 0.5 SD threshold for the SF-36, a change of ≥ 5 points in PCS and MCS has been proposed to be clinically meaningful (23).
Fatigue Scale for Motor and Cognitive Functions (FSMC) (19)	The FSMC includes a cognitive scale and a physical (motor) scale, each consisting of 10 items. Items are scored using a 5-point scale ranging from 1 to 5, yielding a total score range of 20 (no fatigue at all) to 100 (severest grade of fatigue). Based on cut-off values for severity categories, a change from baseline of ≥ 10 in FSMC sum score, ≥ 6 in cognitive subscore, and ≥ 5 in physical subscore should denote a clinically meaningful change.
Work Productivity and Activity Impairment Questionnaire for Multiple Sclerosis (WPAI-MS v2.1) (20)	The WPAI-MS German v2.1 consists of 6 items across 4 domains: absenteeism (work time missed), presenteeism (impairment at work/reduced on-the-job effectiveness), work productivity loss (overall work impairment/absenteeism + presenteeism), and activity impairment. Each domain is measured on a scale of 0% to 100% impairment. The recall period is 7 days. A lower score on the WPAI-MS v2.1 subscales indicates less impairment (i.e., an improvement).

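### The MSQOL-54 'and/or' rules let one patient count as both improved and worsened; the FSMC domain rules in Table 3 need reconciling with the text

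*Protocol article*

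**What the plan says.** **MSQOL-54.** Table 3 (secondary endpoints, QoL) gives two responder rules: "Increase of ≥ 5 points in PCS and/or MCS (improved") and "Decline of ≥ 5 points in PCS and/or MCS (worsened"). The section Endpoints and Assessments describes the same endpoint as "increase (improvement) or decrease (worsening) of ≥5 points] (23) in PCS or MCS score". Neither place says what happens to a patient whose two composites move in opposite directions, and neither names a stable class.

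**FSMC.** Table 3 (Fatigue) has a sum-score rule of 10 points, which stands alone, and two domain rules: "Decline of ≥ 6 points or ≥ 5 points in cognitive and/or physical domain, respectively (improved") and "Increase of ≥ 6 points or ≥ 5 points in cognitive and/or physical domain, respectively (worsened"). Endpoints and Assessments lists the domains one at a time, beginning with the "proportion of patients with decrease (improvement) or increase (worsening) of ≥6 points in the cognitive domain" and then giving the physical domain its own proportion at 5 points.

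**SDMT, for comparison.** The same Table 3 classifies the SDMT on one score, with a residual stable class for patients who meet neither the improved nor the worsened definition.

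**Analysis.** Under Statistical Methods all of this is descriptive, without hypotheses or P values. Mean changes from baseline in PCS, MCS and the FSMC scores are reported alongside the proportions.

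**The concern.** Readers take improved and worsened as exclusive outcomes for a patient. The MSQOL-54 rules do not deliver that, because each is met when either composite passes its cut. Two consequences follow from the wording alone: discordant patients are counted twice, and each rate is the probability of a union of two events, which exceeds the rate on either composite unless the two sets of responders coincide or are nested.

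The Introduction says that these real-world data, including patient-reported QoL outcomes, support the German Health Technology Assessment. The study has no control group, so no comparator shares the same two-chance rule and puts the rate in proportion. A reader who takes the either-scale figure as a rate of improvement on a composite would overstate it, and would overstate worsening in the same way.

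For the FSMC the issue is smaller. The table and the text can yield different proportions from the same data, and the article does not say which is meant.

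**Working it through.** The plan states no responder rate, SD or correlation for these endpoints, so there is no figure of its own to reproduce. The check has a logical part, which needs no assumption, and an illustration, which does.

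**1. Worked patients under the stated rules**

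| Patient | Improved? | Worsened? |
|---|---|---|
| PCS +6, MCS −6 | yes (PCS ≥ +5) | yes (MCS ≤ −5) |
| FSMC cognitive −6, physical +5, Table 3 read as one composite | yes (cognitive ≤ −6) | yes (physical ≥ +5) |
| Same FSMC patient, domains listed separately as in the text | cognitive: yes; physical: no | cognitive: no; physical: yes |
| Same FSMC patient, sum score: −6 + 5 = −1 | no | no |

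Within any single score, nobody can be in both classes. The double count arises only when two scores are joined.

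**2. Direction**

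Let A be a PCS gain of at least 5 points and B an MCS gain of at least 5 points. Then P(A or B) = P(A) + P(B) − P(A and B) ≥ max{P(A), P(B)}. The same holds for declines, so both either-scale rates are at least the larger single-scale rate, whatever the data.

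**3. Size (illustrative)**

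From the plan: the 5-point cut on each composite. Assumed: bivariate normal changes, mean change 0, equal SD of change s on both composites, and correlation r between the PCS and MCS changes.

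- Single-scale rate: P(Z ≥ 5/s)
- Either-scale rate: 2 × P(Z ≥ 5/s) − P(both composites up by ≥ 5)
- Share in both classes: 2 × P(one composite up by ≥ 5 and the other down by ≥ 5)

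For s = 10 and r = 0.5:

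- Single-scale: P(Z ≥ 0.5) = 30.85%.
- Both composites up: 16.33%.
- Either-scale: 2 × 30.85 − 16.33 = 45.4%, the same for improvement and worsening by symmetry.
- In both classes: 7.3%.

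| s | r | Single-scale | Either-scale, each direction | In both classes | Improved + worsened |
|---|---|---|---|---|---|
| 8 | 0.3 | 26.6% | 42.7% | 8.1% | 85% |
| 8 | 0.9 | 26.6% | 32.5% | <0.1% | 65% |
| 10 | 0.3 | 30.9% | 48.3% | 11.8% | 97% |
| 10 | 0.5 | 30.9% | 45.4% | 7.3% | 91% |
| 10 | 0.7 | 30.9% | 41.9% | 3.0% | 84% |
| 10 | 0.9 | 30.9% | 37.2% | 0.2% | 74% |
| 15 | 0.5 | 36.9% | 52.6% | 13.0% | 105% |
| 20 | 0.3 | 40.1% | 59.6% | 23.2% | 119% |
| 20 | 0.9 | 40.1% | 47.1% | 2.4% | 94% |

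Over s = 8–20 and r = 0.3–0.9 the excess of the either-scale over the single-scale rate runs from 5.9 points (32.5 − 26.6) to 19.4 points (59.56 − 40.13). The overlap almost vanishes at high correlation; the excess shrinks but stays at about 6 to 7 points.

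**4. FSMC, only if Table 3 is read as one composite**

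For an assumed SD of change of 6 in each domain, the separate rates are P(Z ≥ 6/6) = 15.9% (cognitive) and P(Z ≥ 5/6) = 20.2% (physical). The 'and/or' rate is 30.6%, 28.7%, 26.4% and 23.1% at correlations 0.3, 0.5, 0.7 and 0.9, with 2.9%, 1.2%, 0.2% and under 0.1% of patients in both classes.

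**The case against.** **The table is shorthand.** An article condenses its endpoints, and the parallel FSMC line is spelled out in the text as separate proportions. The MSQOL-54 line may be meant the same way, with details left to an analysis plan that is not shown. For the FSMC this largely stands: the word 'respectively' ties each cut to its own domain, and the text gives separate proportions that cannot double count. A reader might infer that the FSMC results will be double counted; the article does not support more than a discrepancy between table and text. For the MSQOL-54 it does not rescue the rule, because there the text repeats the 'or' instead of separating the composites. The rule is stated and faulty as stated, rather than merely left open.

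**Nothing favours the drug.** An either-scale rate is a different quantity from a single-scale rate, and it rises for worsening as well as improvement. This stands. A reader might infer a bias in favour of ozanimod; none is shown.

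**The stakes are modest.** The endpoints are secondary and descriptive, mean changes are reported beside them, and no decision rule rests on the proportions. The Introduction mentions QoL outcomes as support for the assessment but not responder proportions. This stands and limits the weight of the point.

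**The 5-point cut.** A reader might also infer that the cut is wrong because it comes from another instrument. Table 4 discloses the origin, "Using the 0.5 SD threshold for the SF-36, a change of ≥ 5 points in PCS and MCS has been proposed", and cites a source. Five points is half an SD only if the SD is 10, but the article gives no SD for the MSQOL-54 composites, so it cannot be shown that the cut is wrong for them. Replacing a fixed, cited cut by one computed from this study's own SD would be a debatable preference. No objection to the cut is raised here.

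**Conclusion.** The point holds for the MSQOL-54. The improved and worsened rules are not mutually exclusive, and both either-scale rates are at least the larger single-scale rate. These two statements follow from the wording and rest on no assumption.

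The size is illustrative only. It depends on assumed normal changes, no mean change, equal SDs of 8–20 and correlations of 0.3–0.9, and these ranges are not bounds on what the study will show. Within them the excess over a single-scale rate is roughly 6 to 19 points in each direction, and the overlap runs from negligible to nearly a quarter of patients.

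For the FSMC the conclusion is limited to an inconsistency between Table 3 and the text. Overall this is a definition worth correcting before the responder tables are produced, not a threat to the primary endpoint or to the mean-change analyses.

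**What to change.** Drop 'and/or' from the MSQOL-54 and FSMC domain rows of Table 3, and the 'or' between PCS and MCS in the text. Report PCS and MCS separately. Report FSMC sum, cognitive and physical scores separately, so that Table 3 agrees with the text. Within each score use three exclusive classes (improved, stable, worsened), with stable as the residual class, as Table 3 already does for the SDMT. The cut-offs stay as they are.

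The cost is a change of wording and about one extra line per table. No new data are needed. Both the improvement and the worsening proportions will be smaller than under the either-scale rule, or at most equal to them.
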